## Radiotherapy

### Positioning and CT/MRI Simulation

All patients will be placed in supine position with thermoplastic mask for whole-brain immobilization. Contrast-enhanced CT simulations are recommended. The slice thickness of the scan should be ≤ 5 mm, and the scanning range should extend from 2 cm above the skull to the lower margin of the 7th cervical vertebra, including the entire cranial and neck. When PCI with hippocampal avoidance is required, a MRI simulation of the brain is strongly recommended and the thickness of the brain MRI scanning should be 1 mm.

### Definition of radiation target volume

The entire brain is contoured as the clinical target volume (CTV), and the CTV is expanded by 0.3 cm to create the planning target volume (PTV) which is named PTV-Brain. The PTV of hippocampal avoidance PCI is named PTV-HA. PTV-HA is PTV-Brain minus hippocampi. Critical organs at risk (OAR) include the bilateral lenses and eyeballs. For patients who are eligible for brain MRI simulation, bilateral hippocampi should be contoured.

### Radiation dose and planning evaluation

The prescribed dose for PTV is 2.5 Gy per fraction, once daily, 5 days a week for two weeks. The minimum requirement for the radiation technique is three-dimensional conformal radiotherapy. If PCI with hippocampal avoidance is required, the minimum requirement for irradiation method is stated to be IMRT. Helical tomotherapy is recommended if available.After completing the radiation treatment planning, the dose distribution in the target volume and the dose to OAR are evaluated. The dose-volume histogram (DVH) is used as a fundamental tool, and the dose distribution in the PTV and OAR is assessed based on the distribution of dose curves in three-dimensional space. The prescribed dose is determined based on the dose received by 95% of the PTV, with dose uniformity ranging from 94 to 106%. The dose constraints for OAR are as follows: lenses: Dmax < 9 Gy, Dmean < 5 Gy; hippocampi: Dmax < 16 Gy, Dmean < 9 Gy.

### Toxicity evaluation

Treatment related toxicities will be evaluated in accordance with Common Terminology Criteria for Adverse Events (CTCAE) 5.0 criteria. (1) Complete blood counts and physical examinations will be performed at least once a week during radiation therapy. (2) Adverse events related to the nervous system will be documented at least once a week during radiation therapy and during follow-up. Hopkins Verbal Learning Test will be used to assess cognitive function.

### Tumor response evaluation criteria and definition of survival time

Tumor response will be evaluated according to Response Evaluation Criteria in Solid Tumors (RECIST) 1.1 criteria.

Brain metastasis-free survival (BMFS) is defined as the time from the start of treatment to BM or death from any cause. Progression-free survival (PFS) is defined as the time from the start of treatment to disease progression or death from any cause. Overall survival (OS) is defined as the time from the start of treatment to death from any cause.

### Follow-up

All enrolled patients will be followed up starting from the start of PCI and continuing for 2 years or until death. Follow-up will be conducted once every three months. At each follow-up, patients routinely received examination of brain enhanced MRI, chest and abdomen enhanced CT, and lung tumor markers. After two years, the frequency of follow-up is left to the discretion of the doctor in charge.

### Radiotherapy for brain metastasis

For patients with ≤ 5 intracranial metastases and a maximum diameter of ≤ 3 cm for a single metastasis, SRS or Cyber Knife radiotherapy will be recommended. Otherwise, WBRT will be administered, especially for patients who have not yet received PCI. For patients who have received PCI and developed BM, SRS or Cyber Knife will be recommended.

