**Methods:**

A multicenter, prospective, randomized controlled study was designed. The key inclusion criteria were: histologically or cytologically confirmed small cell carcinoma, age ≥ 18 years, KPS ≥ 80, limited-stage is defined as tumor confined to one side of the chest including ipsilateral hilar, bilateral mediastinum and supraclavicular lymph nodes, patients have received definitive thoracic radiotherapy (regardless of the dose-fractionation of radiotherapy used) and chemotherapy, evaluated as complete remission (CR) of tumor 4–6 weeks after the completion of chemo-radiotherapy. Eligible patients will be randomly assigned to two arms: (1) PCI and brain MRI surveillance arm, receiving PCI (2.5 Gy qd to a total dose of 25 Gy in two weeks) followed by brain MRI surveillance once every three months for two years; (2) brain MRI surveillance alone arm, undergoing brain MRI surveillance once every three months for two years. The primary objective is to compare the 2-year brain metastasis-free survival (BMFS) rates between the two arms. Secondary objectives include 2-year overall survival (OS) rates, intra-cranial failure patterns, 2-year progression-free survival rates and neurotoxicity. In case of brain metastasis (BM) detect during follow-up, stereotactic radiosurgery (SRS) will be recommended if patients meet the eligibility criteria.

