## Methods

### Study design and objective

This is a prospective, randomized controlled study that includes patients with limited-stage SCLC who achieve CR after definitive chemoradiotherapy. Eligible patients will be randomly assigned to two arms:

Control arm: Patients receive PCI and regular brain MRI surveillance.Study arm: Patients receive regular brain MRI surveillance alone.

If BM is detected during follow-up, SRS is recommended when appropriate.

The primary endpoint is to compare the 2-year brain metastasis -free survival (BMFS) rates between the two arms. Secondary endpoints include 2-year OS, intra-cranial failure patterns, 2-year progression-free survival (PFS), cognitive functions(Hopkins Verbal Learning Test will be used to assess cognitive function).

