### Statistical analysis & sample size considerations

The study is designed as a prospective, randomized controlled non-inferiority trial. Based on previous study results, we hypothesize that the 2-year BMFS rate in the control group is 83%, and the 2-year BMFS in the study group is 68%, which is deemed acceptable as non-inferior. With a power of 80% and a one-sided significance level of 0.025, considering a shedding rate of 10%, 110 patients will be required in each group.

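### The salvage section gives two conflicting instructions for patients who had PCI and develop brain metastases beyond the SRS limits

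*Protocol article*

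**What the plan says.** The detailed rule is in the protocol article under *Radiotherapy for brain metastasis*, in three sentences.

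- First, the limits within which focal treatment is advised: "For patients with ≤ 5 intracranial metastases and a maximum diameter of ≤ 3 cm for a single metastasis, SRS or Cyber Knife radiotherapy will" (the sentence ends by advising it).
- Second, everything outside those limits: "Otherwise, WBRT will be administered, especially for patients who have not yet received PCI".
- Third, patients with prior PCI: "For patients who have received PCI and developed BM, SRS or Cyber Knife will be recommended".

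Two general statements stand elsewhere. The abstract (Methods) says that "stereotactic radiosurgery (SRS) will be recommended if patients meet the eligibility criteria", and *Study design and objective* says "If BM is detected during follow-up, SRS is recommended when appropriate". Neither mentions prior PCI.

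On endpoints, "Brain metastasis-free survival (BMFS) is defined as the time from the start of treatment to BM or death from any cause", and "Secondary endpoints include 2-year OS, intra-cranial failure patterns, 2-year progression-free survival (PFS), cognitive functions".

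**The concern.** The second and third sentences of the salvage section overlap. A patient who had PCI and has more than five lesions, or a lesion larger than 3 cm, is sent to WBRT by one and to SRS or Cyber Knife by the other. The article does not say which prevails.

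The overlap concerns only patients who have had PCI, in practice the control arm. The rule is clear for PCI-naive patients and for anyone within the limits.

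Salvage is part of the strategy under test: the Background and the abstract's Discussion argue that omitting PCI is tolerable because treatment with SRS or WBRT once BM appears does not harm OS. In a multicentre trial, an instruction that can be read two ways in one arm allows that arm's salvage to depend on the site. Under one of the readings, a patient whose whole brain has already been irradiated would have it irradiated again.

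**Working it through.** **1. The instructions side by side**

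| Patient with BM | First sentence | Second sentence | Third sentence | Result |
|---|---|---|---|---|
| No PCI, within limits | SRS/Cyber Knife | – | – | clear |
| No PCI, beyond limits | – | WBRT | – | clear |
| Prior PCI, within limits | SRS/Cyber Knife | – | SRS/Cyber Knife | clear |
| Prior PCI, beyond limits | – | WBRT | SRS/Cyber Knife | conflict |

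The second sentence says *especially*, not *only*, so it keeps patients with prior PCI inside the WBRT instruction. Within the limits, the third sentence only repeats the first. The one place where it adds anything is beyond the limits, where the second sentence says something else.

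**2. Which endpoints can be reached by salvage**

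- BMFS: ends at the first BM or death, so salvage cannot change it.
- PFS: BM is itself progression, so the event has occurred before salvage starts.
- Intracranial failure pattern: at first failure it is fixed before salvage. Only later failures could be affected, and the article does not say whether they count.
- OS and cognition after BM: can be affected.

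**3. Arm size**

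The design states that "we hypothesize that the 2-year BMFS rate in the control group is 83%, and the 2-year BMFS in the study group is 68"%, an implied margin of 83 − 68 = 15 points. With true rates of 83% in both arms, one-sided alpha 0.025 and power 80%:

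n = (1.960 + 0.842)² × 2 × 0.83 × 0.17 / 0.15² = 7.85 × 0.2822 / 0.0225 ≈ 98.4, so 99 per arm; 99 / (1 − 0.10) = 110.

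The stated 110 per arm reproduces. It serves here only as the base for the count below.

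**4. How many patients**

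Inputs: 110 randomised or 99 evaluable per arm; BM rate 16.2% (PCI patients in the sponsor's post-hoc analysis, Background) or at most 17% (100% − 83%, the design's 2-year BMFS events, which include deaths); share of BM beyond the limits 10% to 50% (assumption, not in the article).

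- Patients with BM: 0.162 × 110 = 17.8. Range: 0.162 × 99 = 16.0 to 0.17 × 110 = 18.7.
- Beyond the limits, at 17.8: 0.10 × 17.8 = 1.8 to 0.50 × 17.8 = 8.9, so about 2 to 9 patients.
- As a share of the arm: 0.162 × 0.10 = 1.6% to 0.17 × 0.50 = 8.5%.

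**5. Possible shift in 2-year OS, control arm**

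Suppose the choice of salvage changes 2-year survival in the affected patients by 10 to 30 points (assumption), all in one direction.

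- Low: 0.17 × 0.10 × 10 points = 0.17 points.
- High: 0.17 × 0.50 × 30 points = 2.55 points.

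For comparison, take 2-year OS of 40% to 60% in both arms (assumption). The standard error of the difference with 110 per arm is √(2 × p(1 − p)/110): √(0.48/110) = 6.6 points at 40% or 60%, and √(0.50/110) = 6.7 points at 50%. Even the high case is 2.55 / 6.6 = 0.39 of a standard error.

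**The case against.** The strongest reply is that the section runs from general to specific: SRS within the limits, otherwise WBRT, then a separate provision for patients who had PCI. Read as an exception, the third sentence governs and there is no conflict. That reading is possible. But the article does not state it, and *especially* counts against it: if patients with prior PCI never came under the second sentence, everyone there would be PCI-naive and the word would do no work.

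A second reply is that salvage is discretionary anyway. SRS is only recommended, and the Discussion stresses individual patient factors. This stands as a limit on the consequences, since some variation between sites would exist under any wording. It does not remove the conflict, because the second sentence is phrased as a firm instruction.

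Three stronger readings are tempting, and the article does not support them.

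- A reader might infer that the abstract offers a third, competing rule. It does not. The abstract and the design section are one-line summaries compatible with the detailed rule; they merely fail to settle it.
- A reader might infer that salvage will differ by site and will distort the secondary results. The article shows neither. Variation is possible, the affected group is small, and the OS shift computed above is well inside sampling error.
- A reader might count the absence of data fields for lesion number, size and salvage, or of an analysis by salvage received, as a further defect. Such detail belongs to the full protocol, the case report form or the SAP, which are not shown.

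**Conclusion.** The inconsistency is real and narrow. For patients who had PCI and have BM beyond five lesions or 3 cm, two adjacent sentences give different instructions, with no stated precedence and nothing elsewhere in the article to resolve it.

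The primary analysis is not threatened, and PFS is not either. About 2 to 9 of 110 control-arm patients could be affected. This count rests on the 16.2% incidence carrying over from the sponsor's previous cohort and on the assumed 10% to 50% share beyond the limits. On the further assumption of a 10- to 30-point survival effect, control-arm 2-year OS would move by about 0.2 to 2.6 points. Later intracranial failure and cognition could also be influenced in that small group, by an amount the article does not allow one to estimate.

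The main reason to act is that an investigator facing such a patient needs one instruction, and the choice decides whether the whole brain is irradiated a second time.

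**What to change.** The clinical lead should reconcile the second and third sentences of *Radiotherapy for brain metastasis* into a single unambiguous instruction for BM after PCI beyond the stated number and size limits. Which instruction that should be is a clinical decision on which this review takes no position.

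The cost is one clarified paragraph, circulated to sites before such cases arise. Sample size, endpoints and the primary analysis stay as they are.

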## Discussion

SCLC tends to develop early distant metastasis. Brain is a common site of metastasis in SCLC patients, with approximately 25% of patients present with brain metastases at the time of initial diagnosis [5]. Due to the presence of the blood-brain barrier, conventional chemotherapy drugs have limited efficacy in penetrating brain tissue, making it a potential “sanctuary” for small brain metastatic lesions. Therefore, PCI does not truly “prevent” the development of BM, it plays a role of eliminating potentially but undetectable small metastasis in brain.

With the advances in comprehensive treatment, the prognosis of limited-stage SCLC patients has improved, the probability of BM has also increased correspondingly. Among patients who achieved CR after treatment, the incidence of BM within 2 years was 67%, with the brain being the first site of metastasis in 45% of cases [8].

A meta-analysis demonstrated that in patients who achieved a complete response (CR) after chemoradiotherapy, PCI could significantly reduce the incidence of BM by 25.3% (*P* < 0.001) compared to the control group. Additionally, it was associated with a 5.4% improvement in 3-year overall survival rate (*P* = 0.01) [3].

However, due to the limitations of the meta-analysis, and with the availability of MRI for regular surveillance of BM, the role of PCI in improving OS in SCLC patients is being challenged.

A prospective randomized study conducted by EORTC demonstrated that extensive-stage SCLC patients who received PCI had significantly better outcomes compared to the observation group (1-year incidence of symptomatic BM: 14.6% vs. 40.4%; median survival time: 6.7 months vs. 5.4 months; 1-year overall survival rate: 27.1% vs. 13.3%) [9]. However, one of the major limitations of this study was the absence of pre-PCI brain MRI. In contrast, a phase III randomized study showed that in extensive-stage SCLC patients who have ruled out BM with MRI, PCI did not have a positive impact on OS, compared to the observation group [10].

Traditionally, WBRT is recommended for SCLC patients with BM. A recent large cohort study [11] compared the outcomes of SCLC patients with BM who received SRS or WBRT. The results showed that those treated with SRS had a median survival time of 8.5 months and a time to central nervous system progression (TTCP) of 8.1 months, while patients with a solitary BM treated with SRS had a median survival time of 11.0 months, and those treated with WBRT had a median survival time of 5.2 months. Although WBRT improved TTCP, it did not improve OS. Furthermore, after adjusting for prognostic factors, the OS results favored SRS.

Another study showed that in limited-stage SCLC patients who underwent MRI surveillance after definitive chemoradiotherapy, the occurrence of BM and survival rates did not significantly differ between patients who received SRS for detected BM and those who received PCI [12]. The survival benefit was attributed at least partially to SRS, reducing the contribution of PCI to survival. Although PCI is still recommended based on previous studies, these benefits may be diminished if MRI and SRS are available for diagnosis and treatment.

These findings challenge the traditional approach of using WBRT or PCI for all SCLC patients with BM and suggest that SRS guided by MRI surveillance could be a viable alternative in selected cases. However, it is important to consider individual patient factors, tumor characteristics, and treatment goals when determining the most appropriate management strategy.

Pezzi et al. [13] reported that in patients with limited-stage SCLC who had BM excluded by MRI were matched using a propensity score, although the 3-year incidence of BM was higher in the non-PCI group than in the PCI group, the difference was not statistically significant (20.4% vs. 11.2%, *P* = 0.10). Also, whether PCI was performed or not did not affect the overall survival (HR: 0.84, 95% CI: 0.604–1.180, *P* = 0.32).

Similarly, Qi et al. [14] conducted a retrospective matched analysis of 150 patients with limited-stage SCLC. The results showed a significantly lower 3-year cumulative incidence of BM in the PCI group compared to the non-PCI group (14.7% vs. 22.7%, *P* = 0.007), but there was no significant difference in median survival time between the two groups (35 months vs. 28 months, *P* = 0.128).

Of note, PCI potentially leads to acute and late neuro-toxicities. A pooled analysis of the RTOG 0212 and 0214 showed that patients who received PCI had reduced cognitive function as measured by the Hopkins Verbal Learning Test at the 6-month and 12-month follow-up, compared to baseline (*P* = 0.002). Patient-reported cognitive decline was even three times higher (*P* < 0.0001) [15]. A survey indicated that 38% of limited-stage SCLC patients who did not receive PCI had concerns about the side effects [16].

At present, there is no prospective randomized controlled study on PCI versus regular MRI follow-up after definitive radio-chemotherapy for limited-stage SCLC available. However, several similar studies are underway. SWOG S1827 [17] is a phase III prospective randomized controlled study that aims to enroll patients with limited-stage SCLC who have received radical therapy and patients with extensive-stage SCLC who have responded to systemic therapy. The study will randomize patients into two groups: one group will receive PCI plus regular brain MRI follow-up, while the other group will receive only regular brain MRI follow-up. The primary objective of the study is to compare the two-year survival rates between the two groups. The PRIMA Lung Study [18] is conducted by EORTC, has similar study design, aims to investigate whether brain MRI surveillance alone is non-inferior in terms of OS compare to PCI followed by brain MRI surveillance in both limited and extensive-stage SCLC patients. Another Chinese study [19] recruits and randomize limited-stage SCLC patients who achieve remission after first-line chemoradiotherapy to PCI or MRI surveillance. The primary end point is OS at two years.

In conclusion, with the widespread use of brain MRI, the favorable prognosis of SRS for treating SCLC BM, and the insights gained from the Japanese prospective study on PCI in extensive-stage SCLC, as well as the emphasis on the quality of life of long-term survivors, it is worthwhile to conduct a prospective randomized study comparing active brain MRI surveillance alone with PCI after chemoradiotherapy for limited-stage SCLC. The results of this study are highly likely to change current clinical practices.

## Data Availability

Not applicable.
